#### **8.4 Withdrawal of individual subjects**

Subjects can leave the study at any time for any reason if they wish to do so without any consequences. The investigator can decide to withdraw a subject from the study for urgent medical reasons.

##### **8.4.1 Specific criteria for withdrawal (if applicable)**

Not applicable.

#### **8.5 Replacement of individual subjects after withdrawal**

We follow an 'intention to treat' strategy and have no intention to replace subjects after withdrawal.

**8.6 Follow-up of subjects withdrawn from treatment**

Not applicable.

**8.7 Premature termination of the study**

Not applicable.

## 9. SAFETY REPORTING

### 9.1 Temporary halt for reasons of subject safety

In accordance to section 10, subsection 4, of the WMO, the sponsor will suspend the study if there is sufficient ground that continuation of the study will jeopardise subject health or safety. The sponsor will notify the accredited METC without undue delay of a temporary halt including the reason for such an action. The study will be suspended pending a further positive decision by the accredited METC. The investigator will take care that all subjects are kept informed.

### 9.2 AEs, SAEs and SUSARs

#### 9.2.1 Adverse events (AEs)

Adverse events are defined as any undesirable experience occurring to a subject during the study, whether or not considered related to the investigational product. All adverse events reported spontaneously by the subject or observed by the investigator or his staff will be recorded.

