These properties mean that sound impulses below the human ear's frequency limit about 20 Hz (also called infrasound) and activate the Pacinian bodies. Infrasound waves pass without significant attenuation through the air, solid and liquid media. A clarification for this is that the abdominal Pacinian bodies, which perceives the infrasound, are able to register a better signal/noise ratio than the ones located in the skin, as the latter is assumed to be constantly exposed to much higher mechanical stresses from the environment. It appears that infrasound with high amplitude affects the human sensory system (via the Pacinian bodies) via Vagal and splanchnic stimulation, that is why an emotional reaction may be observed. It is our experience that most people react to this with a pleasant sensation. However, a few react with unpleasant sensation, i.e. anxiety evocation. The latter reaction may be reverted by habituation with incremental increase of the low frequency intensity.

Currently, Vagal Nerve Stimulation (VNS) is being used for treatment of resistant cases of pain, depression, epilepsy and migraine attacks (4) by an implanted electronic device and an

electrode attached to the Nervus Vagus. Substantial amounts of evidence for this effect have been gathered although the precise mechanism is still unknown (5). One of the theories proposed has been described in Box 1, below. VNS, however, requires an intrusive intervention and has some negative side effects, because of efferent stimulation (6).

HALF-MIS (High Amplitude Low Frequency Music Impulse Stimulation)', is an innovative treatment modality aimed at stimulation of the Pacinian bodies with the use of infrasound to stimulate vagal activity. Previously, substantial effects were demonstrated on reduction of depression. It is, however, expected to be effective when used in pain management as mental symptoms such as fatigue, depression and cognitive deficits are often prevalent in patients with chronic pain. It is expected that these types of symptoms may be alleviated, as well as somatic pain.

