## 2. OBJECTIVES

Primary Objective:

1. To investigate the tolerability and safety of HALF-MIS used in elderly patients with chronic musculoskeletal pain.
2. To investigate the effect on pain of HALF-MIS used in elderly patients with chronic musculoskeletal pain.
3. To investigate the effect on central sensitization of HALF-MIS used in elderly patients with chronic musculoskeletal pain.

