### 3. STUDY DESIGN

#### Study design

Placebo controlled pilot study in 60 patients with a chronic musculoskeletal pain syndrome. 30 patients per center will be recruited and screened through one of the participating centers: 1) University Hospital of Copenhagen, Denmark; 2) Anesthesiology Pain Center, University Medical Center Groningen, The Netherlands. The primary examination must result in a cumulated NRS score of more than 3. After randomization there will be a treatment and a control group.

Every patient in the treatment group will receive eight HALF-MIS treatments and the control group eight placebo treatments in three weeks. Every (placebo) treatment will be about 20 minutes and all patients in both groups will undergo all the measurements (NRS, CSI, EuroQol 5D-3L, HADS, PDI, QST, ARTS and UTAUT as described below).

For the recruitment procedure, see paragraph 11.2. The first visit concerns a screening visit for which participants will be invited to the research site at Beatrixoord. When eligible, their treatments will be scheduled. Relevant questionnaires will be sent before each visit. The QST measurements will take place before the first treatment session, after the last treatment session and six weeks after the last treatment session. These items will take about 25-30 minutes to be performed. For an overview of performed questionnaires/measurements see the flowchart at the end of this section.

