## 5. TREATMENT OF SUBJECTS

### 5.1 Investigational product/treatment

HALF-MIS is primarily a vibratory and auditory stimulus within the range of normal life exposures. As this is a non-drug, non-invasive, non-electrical treatment, NO serious side effects are associated with HALF-MIS.

Similar low frequency exposure has been a part of some music therapy concepts, namely VAT (Vibroacoustic Therapy) and VAM (Vibroacoustic Music Therapy) for decades. In this context low frequency exposure has been investigated (as a black box) in the treatment of various conditions such as pain, depression and spasticity. The trials consistently reported positive effects of treatment and no lasting side effects. In some trials, symptoms such as dizziness and nausea are reported but they are always dose related and pass after the treatment session. We encountered two cases of lens luxation in patients exposed to a shaking chair installation with extremely powerful 5 Hz shaking. This exposure is not considered comparable to the HALF-MIS bass exposure, as it has no content of frequencies below 20 Hz.

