## 8. METHODS

### 8.1 Study parameters/endpoints

#### 8.1.1 Main study parameter/endpoint per objective

1. Safety and tolerability: (S)AE listings, UTAUT and ARTS
2. Self-reported Pain: NRS
3. Quantitative Sensory Testing: QST

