## 10. STATISTICAL ANALYSIS

### 10.1 Primary study parameter(s)

Objective 1: To investigate the tolerability and safety of HALF-MIS used in elderly patients with chronic musculoskeletal pain our primary study parameters are Safety (listing (S)AEs) and tolerability (UTAUT and ARTS). These parameters will be analyzed descriptively.

Objective 2: To investigate the effect on pain of HALF-MIS used in elderly patients with chronic musculoskeletal pain we use one primary endpoint: (self-reported Pain (NRS). Pain intensity will be analysed as appropriate depending on data distribution with a two-sided 0.05 level of significance (superiority in the Half-Miss group). Effect sizes and 95% confidence intervals will be calculated for the primary and secondary outcome measures. Changes within the treatment groups over time as well as differences between groups will be assessed by intention-to-treat analyses. Also the primary analysis will follow the per protocol principle. Sensitivity analyses will be provided to evaluate robustness of the results with regard to centre effects, HADS and/or pain medication.

Objective 3: To investigate the effect on central sensitization of HALF-MIS used in elderly patients with chronic musculoskeletal pain. The primary outcome measure is QST. We will compare outcomes before and after treatment by parametric (students t-test) or non-parametric (Mann-Whitney) tests.

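### Adverse events enter the record when volunteered or observed, with no routine question at treatment visits, so the brief effects the protocol names are likely to be under-recorded for its first primary objective

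*Protocol*

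**What the plan says.** The first primary objective in Section 2 is "To investigate the tolerability and safety of HALF-MIS used in elderly patients with chronic musculoskeletal pain". Section 8.1.1 gives its main parameters as "Safety and tolerability: (S)AE listings, UTAUT and ARTS", and Section 10.1 adds "These parameters will be analyzed descriptively". The first hypothesis in the Summary is that the intervention is safe and well tolerated.

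Section 9.2.1 defines an event broadly: "Adverse events are defined as any undesirable experience occurring to a subject during the study, whether or not considered related to the investigational product". The collection rule that follows is narrower: "All adverse events reported spontaneously by the subject or observed by the investigator or his staff will be recorded".

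The protocol names reactions that it expects or knows of. Section 5.1 says of some earlier trials with similar low-frequency exposure that "symptoms such as dizziness and nausea are reported but they are always dose related and pass after the treatment session", and the Summary repeats this. Section 1 adds from the team's own experience that "a few react with unpleasant sensation, i.e. anxiety evocation".

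Section 3 lists what is measured: "all patients in both groups will undergo all the measurements (NRS, CSI, EuroQol 5D-3L, HADS, PDI, QST, ARTS and UTAUT as described below". Section 8.3 describes UTAUT as a semi-structured interview held at the six-week follow-up, and ARTS as a questionnaire on satisfaction with osteoarthritis treatment.

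**The concern.** The definition of an adverse event takes in far more than the collection rule is likely to bring in. A patient who feels dizzy or uneasy for some minutes during a session, and is well again by the time the belt is off, may not mention it, and staff may see nothing. Such an event fits the definition but need not reach the list.

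At stake is the conclusion on the first primary objective. A short or empty list could reflect good tolerability or the lack of a prompt, and a descriptive analysis cannot separate the two. Events that were never collected cannot be recovered later. The point also bears on the pilot's purpose: Section 4.4 expects its outcomes to inform further trials, and Sections 6.4 and 11.4 describe the device as a prototype without a full risk management report.

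Collection of adverse events is a protocol procedure that Section 9.2.1 settles. It is not a detail left to an analysis plan.

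**Working it through.** **Step 1: is there a routine question anywhere in the text?**

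- Section 9.2.1 gives two routes into the record: volunteered by the patient, or observed by the investigator or staff.
- The measurement list in Section 3 holds NRS, CSI, EuroQol, HADS, PDI, QST, ARTS and UTAUT. None is described as an adverse-event question or symptom checklist.
- HADS touches on anxiety, but Sections 8.1.3 and 10.2 use it as an other parameter and to control for depression, not for safety collection.
- Section 8.3 adds self-reported pain medication and no event query.

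**Step 2: do the other two parameters of objective 1 fill the gap?**

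- UTAUT does ask about tolerability, but once, six weeks after the last session. That is late for effects that end with the session, and the interview is not described as a source of adverse-event records.
- Section 8.6 marks follow-up of patients withdrawn from treatment as not applicable. A patient who stops early through discomfort is therefore not assured of the interview.
- ARTS concerns satisfaction.

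**Step 3: how large could the shortfall be?** The protocol states no event rate, capture share or safety power, so there is no figure of its own to reproduce. The following is an illustration only.

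- n = 30 active-arm patients (Section 4.4; Section 8.2 gives 15 at each of two centres, 2 × 15 = 30).
- p = true share of patients with a transient effect. Assumed, 3% to 20%.
- c = share of those patients whose effect is recorded. Assumed, 25% to 100%.
- Expected patients listed = n × p × c.
- Chance that no such patient is listed = (1 − p × c)^n.

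Each cell gives expected patients listed / chance that none is listed:

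| p | c = 1 | c = 0.5 | c = 0.25 |
|---|---|---|---|
| 3% | 0.90 / 0.401 | 0.45 / 0.635 | 0.22 / 0.798 |
| 5% | 1.50 / 0.215 | 0.75 / 0.468 | 0.38 / 0.686 |
| 10% | 3.00 / 0.042 | 1.50 / 0.215 | 0.75 / 0.468 |
| 20% | 6.00 / 0.001 | 3.00 / 0.042 | 1.50 / 0.215 |

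For example, p = 10% and c = 0.5 give 30 × 0.10 × 0.5 = 1.5 patients and (1 − 0.05)^30 = 0.215.

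**Step 4: what would an empty list show?** With 0 of 30 recorded, the one-sided 95% upper bound on the recorded rate is 1 − 0.05^(1/30) = 9.5%. The recorded rate is p × c, so the bound on p is 9.5% divided by c: 9.5% at c = 1, 19.0% at c = 0.5 and 38.0% at c = 0.25.

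These chances concern listing no transient effect of this kind. They are not chances of an empty adverse-event list, since the definition also covers unrelated complaints over about nine weeks in patients aged 65 or over.

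**The case against.** The strongest reply has five parts.

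- **Tolerability is actively asked about.** A reader might infer that nobody asks. That is wrong: the UTAUT interview does. What stands against the reply is its timing and that it does not feed the adverse-event record.
- **Staff are close at hand.** A trained researcher mounts the transducer (Section 6.1), and visits last 45 to 90 minutes around a session of about 20 minutes (Section 3). Effects tied to the session arise when staff may well be present, so some will be observed. This stands, but dizziness, nausea and unease are mainly felt, not seen.
- **The figures rest on assumption and on one capture chance per patient.** Each patient has eight sessions. If capture is 30% to 50% per episode and a patient is affected in three sessions, the chance of being listed is 1 − 0.7^3 = 66% to 1 − 0.5^3 = 88%, assuming independence. The loss shrinks when effects recur. This stands, and it is why no size can be claimed.
- **Neither arm is favoured.** A reader might infer a bias towards the active arm. The documents do not support that: the same rule covers both arms of a trial described as double blinded, with 15 patients per arm at each centre. Equal capture scales both arms down. The ratio is kept, while the absolute difference and the information in the comparison shrink.
- **A per-visit prompt may exist elsewhere.** The flowchart is not reproduced in the copy at hand and the case report form is not part of the protocol text. Section 9.2.1 also does not literally say that only these events count. This cannot be excluded, but the rule and the measurement list that can be read contain no prompt.

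**Conclusion.** The point holds as a matter of likelihood. The rule in Section 9.2.1 is passive, no section of the text provides for questioning at treatment visits, and the resulting list is a main endpoint of the first primary objective. The brief, subjective effects the protocol names are the kind such a rule tends to miss, and missed events can only lower the count.

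A reader might go further and conclude that events will certainly be under-counted, or by a stated fraction. The documents do not support that. The direction is well founded. The size rests wholly on assumed values of p and c, and on treating capture as a single chance per patient. Within those assumptions the expected count falls in proportion to the capture share, so half capture halves it.

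No patient is directly endangered by this, and the safety analysis has no test or threshold to distort. It is still worth correcting before the trial runs, because a finding of good tolerability would otherwise rest partly on events that nobody was prompted to report at the time.

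**What to change.** Amend Section 9.2.1 so that one standard, open and non-leading question about new or unpleasant experiences is asked in both arms, in identical words:

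- at every treatment visit, after the session, and also about the time since the previous one;
- at the six-week follow-up.

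State that the answers are recorded as adverse events alongside those volunteered or observed. If the flowchart or the case report form already holds such a question, align Section 9.2.1 with it.

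The cost is about a minute at visits that already take place, plus more non-serious events listed in both arms. The change touches no treatment, dose or clinical rule.

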#### 9.2.2 Serious adverse events (SAEs)

A serious adverse event is any untoward medical occurrence or effect that

- results in death;
- is life threatening (at the time of the event);
- requires hospitalisation or prolongation of existing inpatients' hospitalisation;
- results in persistent or significant disability or incapacity;
- is a congenital anomaly or birth defect; or
- any other important medical event that did not result in any of the outcomes listed above due to medical or surgical intervention but could have been based upon appropriate judgement by the investigator.

An elective hospital admission will not be considered as a serious adverse event.

The investigator will report all SAEs to the sponsor without undue delay after obtaining knowledge of the events.

The sponsor will report the SAEs through the web portal *ToetsingOnline* to the accredited METC that approved the protocol, within 7 days of first knowledge for SAEs that result in death or are life threatening followed by a period of maximum of 8 days to complete the initial preliminary report. All other SAEs will be reported within a

period of maximum 15 days after the sponsor has first knowledge of the serious adverse events.

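### Section 9.2.2 exempts every elective hospital admission from the SAE definition, even when the condition behind it is new or worse since consent

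*Protocol*

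**What the plan says.** Protocol section 9.2.2 lists the criteria that make an untoward medical occurrence serious. One is that it "requires hospitalisation or prolongation of existing inpatients' hospitalisation". The last is a catch-all for "any other important medical event that did not result in any of the outcomes listed above due to medical or surgical intervention", applied at the investigator's judgement. Directly after the list comes the sentence at issue: "An elective hospital admission will not be considered as a serious adverse event".

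The same section attaches reporting duties to the SAE label. The investigator reports every SAE promptly to the sponsor. The sponsor reports fatal or life-threatening SAEs to the METC within 7 days, and all others within 15 days.

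Section 9.2.1 defines an adverse event as "any undesirable experience occurring to a subject during the study, whether or not considered related to the investigational product" and states: "All adverse events reported spontaneously by the subject or observed by the investigator or his staff will be recorded". Section 9.4 requires AEs to be followed until they resolve or stabilise.

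Section 8.1.1 names the main endpoint of objective 1 as "Safety and tolerability: (S)AE listings, UTAUT and ARTS". Section 10.1 says these parameters are analysed descriptively.

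**The concern.** An exemption for elective admissions has a sensible purpose: a hip operation already arranged for long-standing, stable joint disease is not a harm of the trial. The sentence in 9.2.2 goes further. It contains no condition on when the admission was arranged, when the condition began, or whether the condition has changed since consent.

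Participants are 65 or older and have chronic musculoskeletal disease, and section 1 notes frequent co-morbidity. Deterioration in such patients may plausibly lead to a planned rather than an emergency admission. If a site follows the sentence as written, such a case drops out of the SAE category because of how it was scheduled.

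Two things are at stake. One is prompt reporting, because the sponsor and METC deadlines in 9.2.2 apply only to SAEs. The other is the split between serious and non-serious events in the (S)AE listing that objective 1 relies on. Two centres in two countries must also apply the sentence in the same way, and the protocol gives them no definition of elective to work from.

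**Working it through.** No figure in the protocol depends on this sentence and no formula applies. The check is a reading of the relevant sections against each other.

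1. **The general criterion.** Section 9.2.2 covers an occurrence that "requires hospitalisation or prolongation of existing" hospitalisation. It does not separate emergency from elective admission.
2. **The exemption.** The later sentence in 9.2.2 removes elective admissions as a class.
3. **Search for a limit.** Elective admission is mentioned nowhere else in the protocol. Sections 9.2.1 and 9.4, the endpoints in 8.1 and the analysis in 10.1 do not confine the exemption to admissions arranged before consent, to pre-existing conditions, or to unchanged conditions.
4. **Applying the rule as written:**

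| Admission | Condition | SAE on the hospitalisation criterion? |
|---|---|---|
| Not elective | New or worse since consent | Yes |
| Elective | Existed before consent, unchanged | No, the legitimate purpose of the exemption |
| Elective | New or worse since consent | No, although the criterion itself is met |

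The third row is the defect. It differs from the first only in scheduling.

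5. **Other routes to seriousness.** An event in the third row is still an SAE if it is life threatening, causes persistent or significant disability, or is judged an important medical event. The first two cover only part of the possible cases. The last depends on the judgement of the individual investigator, so it narrows the gap without closing it.
6. **What is lost and what is kept.** The event remains an AE under 9.2.1 and is followed under 9.4. It loses the SAE report to the sponsor, the 15-day report to the METC, and its classification as serious in the listing named in 8.1.1 and 10.1.

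The protocol gives no rate of hospital admission, elective or otherwise, so the number of events affected cannot be derived.

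**The case against.** The strongest reply is that a general criterion followed by an exception is a rule with a carve-out, not a contradiction. An admission is a procedure, and the untoward occurrence is the condition behind it. On this view the sentence says only that an elective admission is not in itself an SAE, and most sites would read elective as arranged before enrolment. The event is in any case recorded and followed, and the endpoint is a descriptive listing of AEs as well as SAEs. The rule is also the same in both arms, so the wording creates no bias between them.

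Much of this stands. The sentence is best called an exemption drawn too widely. The event changes category and does not disappear. No between-arm bias follows from the wording itself. What does not stand is reliance on a reading that the protocol does not state. The literal text exempts the admission whatever its cause, and reporting deadlines turn on that text.

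A reader might also infer more than the protocol supports:

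- **That the halt rule is bypassed.** Section 9.1 lets the sponsor suspend the study on sufficient grounds of risk to subjects. It does not require an SAE label, so a recorded AE can trigger it.
- **That the protocol expects almost no SAEs, so that one reclassified event moves an arm of 30 from 0% to 1/30 = 3.3%, and three move it to 3/30 = 10%.** The remark in section 11.4 that SAE risk is negligible follows the text on quantitative sensory testing. The device risk is described separately, as relatively moderate. No count of affected patients has a basis in the protocol, and the 10% also needs all three events in one arm (3/60 = 5% overall).
- **That lens luxation shows the exemption at work.** Section 5.1 reports: "We encountered two cases of lens luxation in patients exposed to a shaking chair installation with extremely powerful 5 Hz shaking". It attributes these cases to another installation that it considers not comparable, and mentions neither seriousness nor admission. That such an event would lead to a planned admission and meet no other criterion is speculation.

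**Conclusion.** The point holds as a defect in a stated rule, and the sentence should be corrected. As written, section 9.2.2 allows a planned admission for a condition that is new or worse since consent to be filed as non-serious, unless another seriousness criterion applies. The consequence is confined to SAE reporting to the sponsor and the METC and to the serious part of the listing for objective 1.

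The size cannot be stated. It depends on how many such admissions occur during the roughly 9 weeks each patient is in the study, and on how many of them meet no other criterion. The protocol informs neither. The conclusion rests on the literal reading of the sentence and on the absence of any limit elsewhere in the protocol. It assumes no particular event rate. The definition governs reporting from the first patient, so it is not a detail that a later statistical analysis plan could settle.

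**What to change.** Replace the sentence in section 9.2.2 with:

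*An elective admission for a condition that existed before informed consent and has not worsened since, whenever it was planned, is not considered a serious adverse event. Any admission, elective or not, for a condition that is new or has worsened since consent is assessed under the hospitalisation criterion.*

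Informed consent is a usable cut-point because section 11.2 places it before screening. The words *whenever it was planned* matter: without them, an admission arranged after consent for a stable, long-standing condition would be left unclassified.

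The same wording should go on any SAE form or site instruction. The cost is this text change, notified to the METC as an amendment under section 12.3 if approval has already been given, and a few more SAE reports.
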